# Synergy of de-walled Ganoderma Lucidum spore powder (GLSP) on targeted therapy in advanced non-squamous non-small cell lung cancer with epidermal growth factor receptor (EGFR) mutant: protocol for a randomized, double-blind, placebo-controlled study

**DOI:** 10.1186/s12906-024-04416-2

**Published:** 2024-03-18

**Keywords:** Non-small cell lung cancer (NSCLC), Repercussions associated with targeted therapy, Ganoderma Lucidum spore powder (GLSP), Randomized controlled trial (RCT), Fatigue, Evaluation of clinical curative effect

## Abstract

**Background:**

Osimertinib is regarded as a promising third-generation epidermal growth factor receptor (EGFR) tyrosine kinase inhibitor (TKI) for advanced non-squamous non-small cell lung cancer (NSCLC) patients who developed T790M. However the adverse effects, primarily fatigue, remain an overwhelming deficiency of Osimertinib, hindering it from achieving adequate clinical efficacy for such NSCLC. Ganoderma lucidum has been used for thousands of years in China to combat fatigue, while Ganoderma Lucidum spores powder (GLSP) is the main active ingredient. The aim of this study is to investigate whether GLSP is sufficiently effective and safe in improving fatigue and synergizing with Osimertinib in non-squamous NSCLC patients with EGFR mutant.

**Method/design:**

A total of 140 participants will be randomly assigned to receive either de-walled GSLP or placebo for a duration of 56 days. The primary outcome measure is the fatigue score associated with EGFR-TKI adverse reactions at week 8, evaluated by the Chinese version of the European Organization for Research and Treatment of Cancer (EORTC) Quality of Life Questionnaire for Cancer Patients (QLQ-C30). Secondary outcomes include evaluation of treatment effectiveness, assessment of quality of life (QoL), and exploration of immune indicators and gut microbiota relationships. Following enrollment, visits are scheduled biweekly until week 12.

**Trial registration:**

China Clinical Trial Registry ChiCTR2300072786. Registrated on June 25, 2023.

## Introduction

According to GLOBOCAN 2020, mortality of advanced lung cancer already accounts for 18.0% of that from overall cancer, and has been on rise constantly [1], despite the progress in systemic anti-tumor therapy for partial control or alleviation [2]. Notably, the advances in targeted therapies, driven by progressive genotype segmentation, have led to a de-chemotherapy era of molecular phenotypic personalization, represented by the third-generation epidermal growth factor receptor (EGFR) tyrosine kinase inhibitors (TKIs) such as Osimertinib, which has improved response rate (RR) to approximately 80% and prolonged median progress-free survival (PFS) to 10 $${\sim}$$ 14 months for the most common Ex19del with T790M [3, 4]. However, 79-88% of cases have suffered from adverse effects, whose toxicity led to multi-organs dysfunction and poor quality of life [5], disrupting the subsequent long-term use of this drug [6].

Fatigue is the most common adverse event reported by more than two-thirds of patients on Osimertinib [7, 8]. The significant correlation has been demonstrated between fatigue and worse overall survival (OS) in those with cancers, that probably attributed to the constant aggravation of fatigue as a result of clinical neglect and absence of invention, ultimately eroding the general state, and even leading to the termination of anti-tumor therapy [9, 10]. Currently, the principal therapies for fatigue include psychiatric medications, erythropoietin supplementation, and non-pharmacological methods such as exercise and psychotherapy [11]. Regrettably, these approaches are far from effective while lead to additional adverse events or induce malignancies [12]. Thus, it is imperative to optimize the efficacy of Osimertinib associated fatigue in non-squamous NSCLC patients with EGFR mutant.

Ganoderma lucidum spore powder (GLSP), one of the effective ingredients of traditional Chinese herb Ganoderma lucidum, is primarily known for its qi replenishing properties. GLSP has a variety of benefits including anti-inflammatory, antioxidant and immunomodulation [13], suggesting its anti-fatigue potential. Besides, GLSP can inhibit tumor progression, by regulating CD4^+^CD8^+^ T cell ratio and macrophage function, especially the expression of PD-1 in TIME.

Therefore, we organized a multi-center, randomized, double-blind, placebo-controlled study to evaluate the synergy of de-walled GLSP on third-generation EGFR-TKIs represented by Osimertinib in advanced NSCLC with EGFR mutant. The objective of the study is to identify the improvement of de-walled GLSP on Osimertinib induced fatigue and general quality of life. In addition, the study also addresses the objective response to Osimertinib, and its safety. Furthermore, we sought to clarify the underlying mechanism of GLSP on the host immunity through liquid biopsy and intestinal flora assay.

## Methods/design

### Study design

This is a multicenter, randomized, double-blind, placebo-controlled clinical trial with significant advantages in its overall design. After a 7-day screening period, 140 eligible participants will be randomly assigned in a 1:1 ratio to either the trial group (de-walled GLSP + Osimertinib) or the control group (placebo + Osimertinib) through the Interactive Web Response System (IWRS). All participants will undergo two cycles of targeted and experimental drug therapy, followed by a one-month follow-up period. Visits are scheduled on the last day of every 14 days after enrollment. The study is scheduled to be open from February 2023 until February 2026. Recruitment will commence in August 2023 and last for a duration of 18 months (Fig. 1).

**Fig. 1 Fig1:**
[figure not shown]
Study process / flow chart

### Settings and participates

Participants will be recruited from thirteen general hospitals located in six different provinces in China, including Beijing Hospital of Traditional Chinese Medicine, Capital Medical University, China-Japan Friendship Hospital, Beijing Friendship Hospital, Capital Medical University, Beijing Chaoyang Hospital, Capital Medical University, Beijing Tongren Hospital, Capital Medical University, Henan Cancer Hospital, the First Affiliated Hospital of Hebei North University, and the First Central Hospital of Baoding City. Additionally, participants will also be recruited from The First Affiliated Hospital of Zhengzhou University, Hubei Provincial Hospital of Traditional Chinese Medicine, Gansu Provincial Cancer Hospital, Beijing Daxing District People’s Hospital and Ningbo Hospital of Traditional Chinese Medicine. Recruitment will be conducted through advertisements or notices posted on the websites and official WeChat accounts of these thirteen hospitals.

The inclusion criteria are as follows: (1) Non-squamous non-small cell lung cancer diagnosed by cytology/histopathology. (2) Clinical staging of inoperable stage IIIA-IV determined through imaging examinations, including chest-enhanced CT, head-enhanced CT/MRI, cervical/supraclavicular lymph node ultrasound/CT, upper abdomen-enhanced CT/B ultrasound, and whole-body bone scan. (3) Driver gene testing with retained tissue specimens after pathological diagnosis or peripheral blood free/tumor DNA (cf/ctDNA) if sufficient tissue specimens cannot be obtained is recommended for epidermal growth factor receptor (EGFR) gene mutations sensitive to 19DEL and 21L858R. (4) Lung lesions must be measurable. (5) ECOG-PS score should not exceed 2 and expected survival should be greater than 3 months. (6) The age range is from 18 to 75 years old. (7) Participants must agree to participate in this study and sign an informed consent form.

The exclusion criteria are as follows:(1) Presence of isolated brain/bone/adrenal metastases to be treated with radiation. (2) Pregnant or lactating women, or with cardiac, pulmonary, hepatic, renal, hematologic, or other systemic severities that are assessed by the investigator to be unsuitable for participation in this study. (3) Known allergy to the study drug. (4) The subject is participating in other clinical trials.

The withdrawal criteria are as follows: (1) Unexpected rapid progression or radiographic confirmation of progression. (2) Complications or coexisting conditions that prevent continued participation in the trial. (3) Serious adverse events occur that make continuation of the trial inappropriate. (4) Erroneous inclusion in the trial was identified. (5) Safety concerns are identified by the investigators. (6) Participants themselves decide to withdraw. Participants have the right to withdraw from the trial during the course of the trial, meanwhile investigators should attempt to identify and document reasons for withdrawal, such as a perceived lack of treatment effect. Some adverse reactions could not be tolerated, unexplained loss to follow-up, etc.

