### Sample size calculation

The modeling calculations were conducted using the PASS 15.0 software, employing a Two-Sample t-test Assuming Equal Variance (bilateral test) with the following parameters: alpha = 0.05, power = 0.90, and N1:N2 = 1:1 ratio. The score of fatigue according to QLQ-C30 is the primary outcome measure of our study. In the FLAURA patient-reported outcome using the same scale, a mean fatigue score of 32.2 ± 24.9 was observed in patients with advanced EGFR-mutated NSCLC treated with Osimertinib [14]. Referring to previous literature, it is considered that the minimum clinically important difference (MID) in fatigue subscale is 11.1 and there exists a range of change between 11.1 and 22.2 points within this threshold value range for clinical significance assessment purposes [15]. The use of de-walled GLSP is assumed to result in at least a 15-point increase in fatigue score, indicating potential clinical significance for this drug intervention approach. By calculating N1 = N2 = 59 cases, we determined that the minimum required sample size would be 118 cases. Considering a dropout rate of 15%, adjusting N1 = N2 = 70 cases yields a minimum sample size requirement of 140 cases.

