### Assessments and time-points

Assessments will be conducted biweekly from the beginning of the study until completion (Table 1).

**Table 1 Tab1:** Trial visit schedule

Study stage		Baseline	Therapeutic period				Follow-up period	
Point of visit			1	2	3	4	5	6
Follow-up time points^a^		7 days before treatment	Day 14 of treatment	Day 28 of treatment	Day 42 of treatment	Day 56 of treatment	Day 14 after treatment	Day 28 after treatment
Time point (days)		-7 to 0	14	28	42	56	70	84
Visit windows (days)		± 3	± 3	± 3	± 3	± 3	± 7	± 7
Informed Consent		×						
Inclusion and exclusion criteria		×						
Demographic data		×						
History of diagnosis and treatment		×						
Blood and stool samples collected		×				×		
Laboratory and aided examination	Liver/ Renal/ Blood/ Urine/ Stoolfunction test	×				×		
	Twelve items of cytokines	×				×		
	Imageological examination	×			×			×
	ECG	×				×		
QLQ-C30/ PFS-CV/ EQ-5D		×	×	×	×	×		×
Evaluation of adverse reactions		×	×	×	×	×		×
AE&SAE		×	×	×	×	×		×
Compliance evaluation		×	×	×	×	×		×
Combination drug		×	×	×	×	×		×

*Abbreviations* ECG electrocardiograph, QLQ-C30 Quality of Life Questionnaire for Cancer Patients, PFS-CV Chinese version of the Piper Fatigue Scale, EQ-5D European Five Dimensional Health Scale, AE adverse events, SAE serious adverse event

^a^Patients will be followed up every two weeks

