#### Safety assessment

Participants will undergo regular monitoring of blood, urine, feces, liver and kidney function, as well as electrocardiograms on Day 0 and Day 28 of the treatment period. Adverse events will be classified according to the National Cancer Institute’s Common Terminology Criteria for Adverse Events (NCI-CTCAE), version 4.03. Any adverse events, serious adverse events, or adverse drug reactions occurring during the study will be documented with details including severity, relevance to this study, duration, relationship to the trial drug, management measures taken and outcome regression. Follow-up visits will continue until the patient’s condition stabilizes or improves.

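### Progression, SAEs and safety concerns end participation in the trial, not only study drug, so the day-56 fatigue score and scheduled safety tests can be lost for outcome-related reasons

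*Protocol article*

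**What the plan says.** All references are to the protocol article.

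- **Settings and participates, withdrawal criteria.** There is one exit route, withdrawal from the trial. The numbered criteria include "Unexpected rapid progression or radiographic confirmation of progression", complications or coexisting conditions, "Serious adverse events occur that make continuation of the trial inappropriate", and safety concerns identified by the investigators. Intolerance is not a numbered criterion. It appears among the reasons to be recorded: "Some adverse reactions could not be tolerated, unexplained loss to follow-up, etc". Stopping study drug is not distinguished from ending data collection.
- **Assessments and time-points, Table 1.** Imaging is marked at baseline, day 42 and day 84. The tests under "Laboratory and aided examination" other than imaging (laboratory panel, cytokines, ECG), and the blood and stool samples, have one post-baseline mark each, at Day 56. QLQ-C30 and AE/SAE are marked at days 14, 28, 42, 56 and 84. The last follow-up column is labelled both "Day 28 after treatment" and day 84.
- **Safety assessment.** Laboratory tests are placed, "as well as electrocardiograms on Day 0 and Day 28 of the treatment period". All AEs and SAEs are to be documented, and follow-up visits continue until the patient's condition stabilizes or improves.
- **Primary outcome.** The endpoint is the QLQ-C30 fatigue score on day 56.
- **Statistical analysis.** A full analysis set, a per-protocol set and a safety set are planned, with multiple imputation. Data of participants who meet the withdrawal criteria are not to enter the analysis.
- **Sample size calculation.** "Considering a dropout rate of 15" per cent, the plan arrives at 70 per arm, 140 in total.

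**The concern.** Some of the events that remove a patient from the trial are related to what the trial measures. Progression and serious toxicity plausibly go with fatigue, and toxicity is what the laboratory tests and ECGs are meant to detect. If meeting a withdrawal criterion also ends scheduled assessment, the day-56 score and the single post-baseline test set are missing for reasons linked to outcome.

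The exclusion sentence in Statistical analysis adds to this, because read literally it also sets aside what was collected before exit. The inflation from 118 to 140 protects the number of completers. It does not protect the comparability of the two groups of completers. Multiple imputation cannot be assumed to repair the loss, since the patients concerned differ systematically from those still under observation.

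**Working it through.** **1. The plan's own figure.** Inputs from Sample size calculation: difference 15, SD 24.9, two-sided alpha 0.05, power 0.90, 1:1 allocation, dropout 15%. The standardised difference is 15/24.9 = 0.602. The two-sample t-test needs 58.9, so 59 per arm (power 0.9006 at 59). Inflation: 59/(1 − 0.15) = 69.4, so 70 per arm and 140 in total. The figure reproduces and this point does not affect it.

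**2. Number leaving at the planned rate.** 0.15 × 140 = 21.

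**3. The sequence as written, for a patient found to progress at the day-42 imaging.**
- Day 42: progression is seen and the first withdrawal criterion is met.
- Day 56, 14 days later: the primary fatigue score falls due after exit. Under Table 1, so do the only post-baseline laboratory panel, cytokines, ECG, blood and stool samples.
- Already collected: QLQ-C30 and AE/SAE records at days 14, 28 and 42. If the Day 28 timing in Safety assessment applies, one laboratory and ECG set as well.
- Analysis: these earlier data are then excluded if the exclusion sentence is read literally.

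**4. How many lack a scheduled post-baseline laboratory and ECG result.** Let d be the dropout proportion. If all exits precede Day 56, the Day 56 count is 140 × d, which is an upper limit. For Day 28, assume exits spread evenly over 56 days: 140 × d × 28/56. Only the 15% is the plan's; the other rates are assumptions to show the range.

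| Dropout | Test day 56 (upper limit) | Test day 28 (even exits) |
|---|---|---|
| 5% | 7 | 3.5 |
| 10% | 14 | 7 |
| 15% | 21 | 10.5 |
| 20% | 28 | 14 |
| 30% | 42 | 21 |

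The Day 56 column also gives the upper limit for missing day-56 fatigue scores, whichever laboratory day applies. Cytokines and biosamples appear only in Table 1, so their count follows that column too.

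**5. Time origin of the follow-up columns.** For 56 days of treatment the two labels agree: 56 + 14 = 70 and 56 + 28 = 84. For a stop on day 20 (illustration), counting from the last dose gives 20 + 14 = 34 and 20 + 28 = 48. The fixed days remain 70 and 84, which are 50 and 64 days after the last dose. Both labels cannot be met.

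**The case against.** The strongest objection is that this is a journal article, and an early-termination visit is something the full protocol may well contain. That stands: the missing exit column is no finding by itself, and the article does not say that no exit assessment is done. The point rests on what is stated: one withdrawal category, imaging two weeks before the primary assessment, and an exclusion sentence tied to the withdrawal criteria.

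A reader might infer that the patients most likely to be harmed have no post-baseline safety data. The documents do not support that. AE/SAE recording is scheduled at days 14, 28, 42, 56 and 84, every event during the study is to be documented, and follow-up visits continue until the condition stabilizes or improves. A patient withdrawn for an SAE has that SAE on record. What is missing is the scheduled laboratory, ECG and biosample result. AE reporting does not fully replace it, because symptom-free liver, renal or blood changes are found only by testing.

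A reader might also infer a bias towards safe and effective. That is not shown. Both arms receive osimertinib, so its toxicity and progression on it cause exits in both. A bias between groups needs exits that differ between arms, in number or in kind. If GLSP reduced fatigue-related exits, the loss could favour placebo.

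Two smaller objections stand in part. The follow-up labels agree for a patient treated for the full 56 days, so the conflict arises only after an early stop. The exclusion sentence follows directly on the per-protocol definition and may have been meant for that set alone, but as printed it carries no such limit and sits badly with a full analysis set and a safety set.

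**Conclusion.** The concern holds in a limited form. Following the stated rules, patients who meet a withdrawal criterion before day 56 lose the primary score and, under Table 1, every scheduled post-baseline laboratory, ECG and biosample result. Their AE/SAE records up to exit exist.

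At the planned 15% dropout this is up to 21 of 140 patients with Day 56 as the test day. That figure assumes that every dropout leaves before day 56. With Day 28 it is about 10 to 11 for laboratory tests and ECG, assuming evenly spread exits. The loss is likely to be related to outcome, but the direction of any bias between groups is unknown. The disagreement between Day 28 and Day 56 is a contradiction in the text and needs correcting in any case. The Table 1 columns were read from cell positions in extracted text.

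The plan should be changed on this point because data not collected cannot be recovered after database lock. Confidence is medium, since the full protocol may already cover part of it.

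**What to change.** 1. In the withdrawal criteria, separate discontinuation of study drug from withdrawal of consent to data collection. The criteria for stopping treatment stay as they are.
2. Keep every patient who has not withdrawn consent in the scheduled assessments, counted from enrolment. These include the day-56 QLQ-C30 and the laboratory tests and ECG on the day finally settled.
3. Seek the outstanding scheduled laboratory tests and ECG at exit only from patients who will not return.
4. Reconcile Day 28 in Safety assessment with Day 56 in Table 1 for laboratory tests and ECG.
5. Give the Table 1 follow-up columns one time origin.
6. Bring the exclusion sentence in Statistical analysis into line, so that data kept under items 1 and 2 are not discarded from the full analysis and safety sets.

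**Cost.** The changes are to protocol wording and table labels. Sites will carry out visits and tests that the present rule would drop, but for a retained patient none beyond what a completer already has. Some patients will decline. Some fatigue scores will be collected off study drug, so the day-56 comparison will include patients who had stopped it.

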### Intervention

The programmatic interventions involve the utilization of Osimertinib, and de-walled GLSP.

#### Third-generation EGFR-TKI Osimertinib

The initial treatment regimen for EGFR-mutated NSCLC involves the administration of third-generation EGFR-TKI Osimertinib, as recommended by the NCCN Clinical Practice Guidelines for NSCLC 2022 V6. A targeted therapy duration of 56 days will be implemented during the study period.

#### De-walled Ganoderma Lucidum spore powder

All participants will commence administration on the first day of enrollment and continue for a duration of 2 months. The drugs should be completely dissolved by stirring at a temperature of 100 °C hot water, diluted with cold water or cooled prior to administration two grams twice per day during the initial week, and four grams twice per day from weeks 2 to 8. In parallel, the control group will receive placebo pellets composed of 95% dextrin and 5% de-walled GLSP following an identical protocol. Both TCM granules and placebos are uniformly manufactured by Zhejiang Shouxiangu Pharmaceutical Co., LTD (located at [name]) to ensure similarity in terms of appearance, smell, texture, and taste. Participants are required to return the kit along with its label to the CRC as evidence of timely medication usage for adherence evaluation.

### Randomization and allocation concealment

The IWRS of the ProResearchCom Intelligent Monitoring System for Clinical Research will be utilized. Upon enrollment of eligible participants, it is obligatory for the Clinical Research Coordinator (CRC) to input participant details into the IWRS. Once verified by either the Principal Investigators (PI) or Sub-Investigator (Sub-I), participants will be allocated to either the trial or control group in a 1:1 ratio. The IWRS will automatically generate unique identification numbers and drug codes for each participant, subsequently providing feedback on grouping results to the PI or sub-I, who will then notify the drug administrator regarding preparation of drugs corresponding to their respective assigned drug codes.

The current study utilizes a double-blind methodology, whereby the de-walled GLSP drinkable tablets and placebo are enclosed in visually indistinguishable cartons utilizing identical pouches. Each carton is allocated a drug number that conceals details regarding the participant’s group and type. Participants will remain unaware of their treatment allocation until the completion of the trial, while statistical analysts have access to complete group information but do not actively partake in the trial.

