#### Secondary outcomes

The secondary outcomes are as follows:

The efficacy evaluation of the combination of de-walled GLSP and EGFR-TKIs will be evaluated based on objective response rate (ORR), disease control rate (DCR), and progression-free survival (PFS) according to RECIST 1.1 criteria. Imaging examinations and efficacy assessments will be conducted on day 0, day 42, and day 84 of the treatment period, calculating ORR/DCR, while PFS will be determined by follow-up at each treatment cycle during the follow-up period.

The QoL assessment will be conducted using the QLQ-C30, PFS-CV (Chinese version of the Piper Fatigue Scale), and EQ-5D (European Five Dimensional Health Scale). Participants will independently complete these three questionnaires with assistance from the investigator to evaluate patients’ QoL from a multidimensional perspective. The total score for QLQ-C30 is calculated by summing scores across domains and dividing by the number of items included, which is further linearly transformed using polarization. PFS-CV measures typical fatigue symptoms and is calculated as the mean sum of all topic scores, with subscale scores obtained by averaging four different dimensions separately. EQ-5D quantifies patient health status through five dimensions assessed via a utility index, while a visual scale allows direct scoring by patients on a scale of 0 to 100. QoL will be collected at baseline and each visit.

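### As described, the IWRS reports the group to the investigator, which contradicts the double-blind label and exposes a subjective primary endpoint to investigator expectation

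*Protocol article*

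**What the plan says.** All of the following is in the Protocol article.

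- **Label.** Randomization and allocation concealment states: "The current study utilizes a double-blind methodology". Study design and the Introduction use the same term.
- **What the IWRS returns.** After generating identification numbers and drug codes, the system goes on "subsequently providing feedback on grouping results to the PI or sub-I". That person's next step is to have the coded drug made ready for the participant.
- **What hides the group.** "Each carton is allocated a drug number that conceals details regarding the participant’s group and type". The Intervention section adds that the product and placebo are made to match in look, smell, texture and taste.
- **Who is said to be blinded.** "Participants will remain unaware of their treatment allocation until the completion of the trial". No other role is named as blinded. Of the analysts it says "statistical analysts have access to complete group information", adding that they take no active part in the trial.
- **How the primary endpoint is collected.** Primary outcome sets the QLQ-C30 fatigue subscale at day 56 as the endpoint. Secondary outcomes says of the QLQ-C30, PFS-CV and EQ-5D: "Participants will independently complete these three questionnaires with assistance from the investigator".
- **Withdrawal and analysis.** The withdrawal criteria, under Settings and participates, include safety concerns identified by the investigators. Statistical analysis excludes the data of any participant who meets a withdrawal criterion.

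**The concern.** A coded-carton design works because site staff need only the code to dispense. If the system also tells the principal or sub-investigator the group, the carton number no longer protects the investigator's blind, and what remains is a participant blind only. The section therefore contradicts itself. This is a point about what the text states, not about detail left out of a condensed article.

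The endpoint makes it matter. The Discussion says a patient-reported outcome was chosen because fatigue is subjective. An investigator who knows the arm and helps a patient with the form can influence the answers through explanation, tone or expectation. There is also a second route: an investigator's safety judgement can lead to withdrawal, and withdrawal removes the participant from the analysis. Either route could create a difference between arms that the product did not cause, and no later analysis can restore a blind once it is lost.

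**Working it through.** **1. The statements side by side**

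| Question | Text in the article | Consistent with double-blind? |
|---|---|---|
| What is the trial called? | "The current study utilizes a double-blind methodology" | Yes |
| What is on the carton? | "Each carton is allocated a drug number that conceals details" | Yes |
| What does the IWRS return to the investigator? | "subsequently providing feedback on grouping results to the PI or sub-I" | No, if read literally |
| Who stays unaware? | Participants only | Incomplete: no statement about investigators |
| Who may help with the primary questionnaire? | The investigator | Safe only if the investigator is blinded |

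The section speaks of allocation to a trial or control group and names drug codes as a separate item. In its own vocabulary a grouping result is therefore most naturally the arm. The next step, preparing the drug by its code, does not need the arm.

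**2. The plan's own figure**

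Inputs from Sample size calculation: SD 24.9, difference 15, two-sided alpha 0.05, power 0.90, 1:1 allocation, dropout 15%.

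- The exact two-sample t-test gives 58.89, so 59 per arm, with power 0.9006 at 59.
- With dropout, 59/0.85 = 69.4, so 70 per arm and 140 in total.

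The stated sample size reproduces. The blinding point does not change it.

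**3. Scale of a possible bias (illustration only)**

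- Standard error at 59 per arm: 24.9 × √(2/59) = 4.58.
- Smallest significant difference: t(0.975, 116) × 4.58 = 1.981 × 4.58 = 9.08 points.

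Assumption, taken from nowhere in the article: knowing the arm moves the score by one step of 11.1 points (the article's minimum important difference) in a fraction f of GLSP participants, and in no controls. The bias is then f × 11.1. The last column is the two-sided rejection rate of the t-test at 59 per arm if the product has no effect (noncentral t with 116 degrees of freedom and noncentrality bias/4.58).

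| f | Bias (points) | Share of 15 | Share of 9.08 | Rejection rate with no true effect |
|---|---|---|---|---|
| 1 in 5 | 2.2 | 15% | 24% | 7.7% |
| 1 in 3 | 3.7 | 25% | 41% | 12.6% |
| 1 in 2 | 5.6 | 37% | 61% | 22.5% |

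The table shows how sensitive the comparison would be to a modest bias. It does not estimate one. The contradiction in step 1 stands without it.

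**The case against.** The strongest defence is that the phrase is loose wording. It sits between two mentions of drug codes, nothing in the dispensing step uses the arm, and the next paragraph describes matched cartons and a concealing number. On that reading the investigator receives only a code and the blind is intact. This is plausible, and it limits the point to the procedure as written. It does not remove it: the published text still says that the group is fed back, and either the sentence or the system setting must be corrected.

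The link to the questionnaire is also partly inferred. The article does not say that the assisting investigator is the one who received the grouping result, and it says that participants complete the forms independently. The person giving the answers stays blinded on any reading. All of this stands. But the same sentence provides for investigator assistance, and nothing separates the two roles.

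Four stronger readings are tempting and are not supported:

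- **That the trial is being run unblinded.** A protocol article describes a plan and is no evidence of conduct.
- **That unblinded analysts will choose the test to suit the result.** The article does give analysts group information. However, Data management sends statisticians only the locked database, and the choice between tests is commonly fixed in an analysis plan that is not shown here.
- **That unblinded investigators judge adverse-event causality.** Safety assessment says the relationship is documented but does not say by whom.
- **That exposed participants could be excluded in a sensitivity analysis.** On the literal reading everyone enrolled before a correction is exposed, so the exclusion would remove all of them.

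**Conclusion.** The point holds for the procedure as described. Feeding the grouping result back to the principal or sub-investigator contradicts the double-blind label and the concealing carton number, and the article names only participants as unaware. Taken literally, this exposes the day-56 fatigue comparison to investigator expectation by two routes: help with the questionnaire, and withdrawals that take data out of the analysis.

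The conclusion rests on reading the phrase as the arm and not the code, and on the absence of any stated separation between the investigator who receives the result and the one who assists. The size of any bias is unknown; the 2.2 to 5.6 points shown are an assumption throughout. The correction is still needed, because the endpoint is subjective and the literal procedure serves no dispensing purpose.

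**What to change.** 1. Establish what the IWRS actually displays. Configure it so that the principal investigator, sub-investigator, CRC and drug administrator receive only the participant number and drug code, with the arm visible only through an emergency-unblinding function.
2. Reword Randomization and allocation concealment to say this, and state that investigators and site staff are blinded until database lock.
3. In Secondary outcomes, specify that any help with the questionnaires is given only by people without allocation access.
4. If the arm has already been released for any participants, document for whom and when, and report it as a limitation.

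The cost is small: a permission setting, a few sentences of protocol text and, if needed, a record of past releases. If step 1 shows that only the code was ever returned, the remaining work is wording. The sample size of 140 does not change.
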